## Abstract

**Introduction:**

This feasibility study aims to develop and test a new model of practice in Australia using digital technologies to enable pharmacists to monitor early signs and symptoms of medicine-induced harms in residential aged care.

**Methods and analysis:**

Thirty residents will be recruited from an aged care facility in South Australia. The study will be conducted in two phases. In phase I, the study team will work with aged care software providers and developers of digital technologies (a wearable activity tracker and a sleep tracking sensor) to gather physical activity and sleep data, as well as medication and clinical data from the electronic medication management system and aged care clinical software. Data will be centralised into a cloud-based monitoring platform (TeleClinical Care (TCC)). The TCC will be used to create dashboards that will include longitudinal visualisations of changes in residents’ health, function and medicine use over time. In phase II, the on-site pharmacist will use the centralised TCC platform to monitor each resident’s medicine, clinical, physical activity and sleep data to identify signs of medicine-induced harms over a 12-week period.

A mixed methods process evaluation applying the RE-AIM (Reach, Effectiveness, Adoption, Implementation, Maintenance) evaluation framework will be used to assess the feasibility of the service. Outcome measures include service reach, changes in resident symptom scores (measured using the Edmonton Symptom Assessment System), number of medication adverse events detected, changes in physical activity and sleep, number of pharmacist recommendations provided, cost analysis and proportion of all pharmacists’ recommendations implemented at 4-week, 8-week and 12-week postbaseline period.

**Ethics and dissemination:**

Ethical approval has been obtained from the University of South Australia’s Human Research Ethics Committee (205098). Findings will be disseminated through published manuscripts, conference presentations and reporting to the study funder.

**Trial registration number:**

ACTRN12623000506695.

STRENGTHS AND LIMITATIONS OF THIS STUDYCombined various sources of health data into a single centralised platform for the residential aged care pharmacist to actively monitor medicine-induced harms.Uses objective assessments of changes in physical activity and sleep to identify ‘mild’ medicine harms.Due to recruiting from a single residential aged care facility in South Australia, findings may not generalise across all residents living in aged care.Lack of compliance with use and wearing of digital technologies by residents is a potential limitation.

## Introduction

Approximately 8% of adults in Australia aged 65 years and older reside in aged-care facilities (nursing home),^1^ with up to 63% receiving nine or more regular medications.^1^ Medicine-related problems contribute to an estimated 250 000 hospital admissions in Australia every year, with an estimated annual cost of US$1.4 billion.^2^ Medicine-related harms are of significant concern in residential aged care, with up to 27 adverse medicine events occurring per 100 residents per month.^3–5^ In Australia, about one in five persons living in residential aged care experience an adverse medicine event every month; of which 83% were potentially preventable.^6^ Despite the significant medicine-related harms, most Australian residential aged care facilities have limited capacity to provide clinical pharmacy services; existing services are limited to government-funded residential medication management review (comprehensive medication reviews performed by accredited pharmacists in residential aged care) and quality use of medicine services.^7^

The Australian Government, recognising the significance of medicine-related problems in aged care, committed US$350 million to improve medication safety in residential aged care through funding for pharmacists.^8^ The government investment presents new opportunities for pharmacists to review residents for signs and symptoms of medicine harms more frequently. The present study builds on our recent randomised controlled trial which investigated the effectiveness of ongoing pharmacist assessments compared with usual care in reducing medicine-induced deterioration, frailty and adverse events across 39 residential aged care facilities in Australia.^9 10^ Our study showed that one in five residents experienced a preventable adverse event (eg, falls, fractures) every month due to medication use.^9^ The pharmacists identified and resolved medicine-related harms and served as an advocate for residents. Furthermore, significant differences in change in cognition from baseline were observed between intervention and control groups.^9^ The service ensured pharmacist engagement with residents, rather than just reviewing medicines, which enabled the advocacy.^11^

Frequent monitoring of medicine-induced harms is important because medicines can cause mild harm (eg, sedation, poor balance) that often remains undetected, but can lead to serious adverse events in older people if left unmanaged. For example, commonly prescribed psychotropic medicines can cause sedation and poor cognition that may lead to injurious falls and fractures.^12^ An increase of sedative load from two to four over a 12-month period has been associated with an average increase in daily sedentary behaviour of approximately 24 min^13^; an increase of 60 min/day of sedentary time is associated with a 19% increase in risk of death.^14^ Detecting mild, cumulative effects of medicine-induced harms, including changes in physical activity, is likely to be important, however, this can be difficult and labour intensive to measure and monitor.

Harnessing digital technologies to enable active monitoring of medicine-related harms is one potential strategy to enabling proactive monitoring. For pharmacists to effectively monitor harms, they will not only need to review medicines, but also recognise and monitor early signs of medicine-induced harms such as changes in sleep, activity or cognition.^9 13^ Digital technologies can measure changes in sleep, activity or cognition objectively, which may enhance effective communication about medicines-related harm across aged care residents’ care teams, including to general practitioners (GPs), nurses and care staff as well as support the recommendations from pharmacists and their acceptance by the team and residents themselves. The TeleClinical Care (TCC) platform has been used successfully during the COVID-19 pandemic to safely manage >8000 COVID-19-positive patients as they self-isolated at home^15^ and is being used in trials to manage cardiovascular disease and stroke.^16^

The ADEPT project aims to develop and implement a digitally enabled, evidence-based, pharmacist service built on TCC (TCC-ADEPT) to actively detect medicine harms in residential aged care. Specifically, we will:

determine the number and proportion of eligible residents who were willing to participate in the study;determine changes in resident outcomes, including changes in symptoms as measured using the Edmonton Symptom Assessment System (ESAS),^17^ physical activity and sleep (24-hour movement behaviour) and adverse events including falls (both injurious and non-injurious), fractures, delirium, faecal impaction, hospitalisation or emergency department presentation due to adverse medication events and medication incidents, predigital and postdigital pharmacist service;determine the number and types of pharmacist recommendations that resulted following use of the TCC-ADEPT platform, and the number of pharmacist recommendations that were accepted and implemented by GPs and aged care staff;explore the acceptability of the digital pharmacist service by residents and family members, aged care staff and GPs;assess the costs associated with implementing the TCC-ADEPT platform and potential cost impacts to the health and aged care system in wider-spread roll out of the platform;explore the residential aged care facility’s intention to continue to implement the pharmacist service poststudy funding and whether the service aligns to the facility’s mission or sustainability of business model.

We hypothesise that the new pharmacist service is feasible and acceptable to aged care staff, residents and their GPs, and can enhance detection of early signs and symptoms of medicine harms, triggering review and action when required.

### Methods and analysis

### Study design

The ADEPT project will be conducted in two phases over a 12-month period. Phase I will include gathering data from digital technologies, medication and health records into the TCC platform. Digital technologies will include an activity tracker^18^ and a sleep sensor.^19^ A pre-post 12-week implementation study will constitute phase II of the project. The on-site pharmacist will monitor all participants using the centralised TCC-ADEPT platform, using data to inform resident reviews and to initiate conversations with residents, GPs and aged care staff on medicine, health and quality of life changes for residents. Recruitment and study implementation will occur from August 2023 until February 2024.

### Patient and public involvement

Aged care residents, representatives and health professionals were directly involved in the development or design of this study. Findings from interviews with residents, carers and aged care staff from the Reducing Medicine-Induced Deterioration and Adverse Reactions (ReMInDAR) trial were used to inform the development and design of this study.^20^

### Cohort selection

Residents will be considered eligible to participate if they are a permanent resident living in the designated residential aged care facility. Exclusion criteria include receiving palliative or respite care.

### Screening and recruitment

Residents will be recruited from an aged care facility in South Australia. Promotional recruitment material (flyers) will be distributed onsite in common areas of the facility 1 month prior to study commencement. Participant information sheets will be provided to residents deemed potentially eligible by facility staff, and will be given to all residents willing to participate, informing them of the study details and pharmacist service.

Study staff will perform initial screening of residents’ care record to identify potentially eligible residents. Screening logs will be kept monitoring residents’ recruitment and to enable a description of the study population from which eligible residents have been enrolled. If the resident fulfils inclusion criteria based on the initial screening process, the on-site pharmacist will invite the resident to participate in the study and written informed consent will be obtained from the resident or their authorised representative (model consent form shown in online supplemental material).

10.1136/bmjopen-2023-080148.supp1Supplementary data

### Baseline data collection

Once written consent is obtained, study staff will collect baseline data from the Resident Care Assessment Record held electronically in Leecare^21^ and Medi-Map^22^ software, which contains demographic details, comorbidities, medicine use, falls history and care provided within the aged care facility. Study staff will administer the ESAS^17^ and the Montreal Cognitive Assessment (MoCA)^23^ at baseline. An observational logbook or diary will be kept to record information not collected in the existing data fields. Table 1 indicates data collected at each data collection time points.

**Table 1 T1:** Data collection schedule

Variable	Description	Data source	Data collection time points			
			Baseline	4 weeks	8 weeks	12 weeks
Demographic	Age, gender	Leecare	✓			
Medical conditions	Diagnosis of medical condition	Leecare	✓	✓	✓	✓
Medications*	Name, strength, dose, frequency of medicine administration	Medi-Map	✓	✓	✓	✓
Nutritional status	Swallowing status	Leecare	✓			✓
Functional ability	Mobilisation status	Leecare	✓			✓
Cognitive function	Montreal Cognitive Assessment	Leecare	✓			✓
Falls history	Number of falls and related health outcomes	Leecare	✓			✓
Vital signs	Height, weight, blood pressure (systolic and diastolic), respirations, pulse, BGL, SpO_2_	Leecare	✓	✓	✓	✓
Pain	PainChek score severity across six domains	Leecare	✓	✓	✓	✓
Residential Medication Management Review (RMMR)	Dates of RMMR provision will be recorded	On-site aged care pharmacist	✓	✓	✓	✓
Physical activity	Time spent in light, moderate, vigorous-intensity activity	Fibion SENS device	✓	✓	✓	✓
Sleep	Movements during sleep, durations of light, deep and REM sleep	Fibion Emfit device	✓	✓	✓	✓
Edmonton Symptom Assessment Scale	Severity across 10 symptoms	Participant or third-party informant review	✓	✓	✓	✓
Adverse events	For example, falls, fracture, delirium, faecal impaction, incontinence	Leecare, pharmacists, aged care staff, residents	✓	✓	✓	✓
Incidents	Medication incidents will be recorded including date/time and severity	Leecare, pharmacists, aged care staff, residents	✓	✓	✓	✓
Ambulance call-outs	Date and reasons will be recorded	Leecare, pharmacists, aged care staff, residents	✓	✓	✓	✓
Hospital visits	Date and reason of emergency department visits or hospital admission will be recorded	Leecare, pharmacists, aged care staff, residents	✓	✓	✓	✓
All-cause mortality	Any deaths in the 12-week study period will be recorded	Aged care staff		✓	✓	✓

*Data will be collected and exported daily into the TCC-ADEPT platform over the 12-week study period.

BGL, blood glucose level; REM, rapid eye movement; SpO_2_, oxygen saturation; TCC, TeleClinical Care.

### Measures

#### Edmonton Symptom Assessment Scale

The ESAS is a 10-item numeric rating scale assessing self-reported pain, fatigue, nausea, depression, anxiety, drowsiness, shortness of breath, appetite, well-being and sleep.^17^ Participants or their carer will rate the severity of each symptom on a scale of 0–10 by circling a number on each scale which best describes their symptoms over the past 24 hours.^17^ Higher scores indicate higher symptom burden.

#### Montreal Cognitive Assessment

The MoCA is a 1-page, 30-point screening instrument that assesses cognitive domains of memory, language, executive functions, visuospatial skills, calculation, abstraction, attention, concentration and orientation.^23^ A cut-off score of 26 has been shown to differentiate mild cognitive impairment or dementia from normal cognition.^23^ When scoring, a 1-point adjustment is given to those with 12 or less years of formal education.^23^

#### Fibion SENS

The activity tracker is the Fibion SENS device (SENS Motion, Copenhagen, Denmark),^18^ which is a waterproof three-dimensional triaxial accelerometer (4.7 cm×2.2 cm×0.45 cm) previously validated for use in older adult samples.^24 25^ The SENS device samples data at a rate of 12.5 Hz and an algorithm categorises data into predefined activities: lying/sitting rest; lying/sitting movement; standing; walking; sporadic walking; cycling and similar of light, moderate and vigorous intensity. Residents will be asked to continually wear the tracker if possible, or for a minimum of 16 hours per day to ensure sufficient data collection. The manufacturer recommends attaching the device to the lateral distal thigh with a medical adhesive patch approximately 10 cm above the lateral epicondyle.

#### Fibion Emfit

The sleep sensor is the Fibion Emfit sensor (Emfit, Kuopio, Finland).^19^ The device is a thin, flexible undermattress device (32 cm×62 cm×0.4 cm) comprising charged polymer layers and air voids, the position of which changes with mechanical pressure to measure body movement.^26 27^ The ballistic forces generated collect activity and physiological data during sleep including sleep time, sleep classes, heart rate, breathing rate, movement and bed occupancy and exits.^27^

### Phase I

#### Dashboard integration

A protocol will be developed for extracting data from digital technologies (wearable activity trackers and sleep tracking sensors) and resident clinical information and medication records into the TCC-ADEPT platform. The TCC-ADEPT platform will include a dashboard with longitudinal visualisations of changes in residents’ health and well-being over time (ie, physical activity, sleep quality, blood pressure, etc) using data loaded from the digital technologies and clinical data (figure 1). Medicine use (including sedative load and cumulative medicines risk calculator) and pathology records (eg, renal function) will also be uploaded to the dashboard. The platform infrastructure will be hosted on the Microsoft Azure cloud service with built-in regulatory compliance for the Health Insurance Portability and Accountability Act, and the Australian Government Information Security Manual. The resulting dashboard will be operated by the on-site pharmacist in phase II (feasibility study).

**Figure 1 F1:**
[figure not shown]
(A) Example of vital signs (blood pressure, body weight and oxygen saturation) with onset of a new medication (alprazolam 0.25 mg three times a day) overlaid in the TCC-ADEPT platform. (B) Example of cumulative risks and type of adverse drug reactions displayed in the TCC-ADEPT platform. CNS, central nervous system; TCC, TeleClinical Care.

#### Identification of triggers for review

To determine whether a resident has experienced medicine-induced harm, the on-site pharmacists will review data from the digital technologies, residents’ clinical and medicine data presented in the TCC-ADEPT dashboard. Baseline data collected within the first 2 weeks of the study will be averaged and serve as the reference point, and the dashboard will present longitudinal data and trends for each resident. To determine whether changes in health and function are medicine-induced, visualisations will be presented relative to each time point where medicines are added, ceased or modified.

In-built data analytics running an automated rules-based algorithm will be used for detection of changes in physiological or other health parameters. If and when residents’ health declines beyond a certain threshold compared with baseline levels, the system will automatically flag residents that will alert the pharmacist (figure 2).

**Figure 2 F2:**
[figure not shown]
Proposed service flow.

The trigger threshold will be determined based on minimum clinically significant difference where known in the literature (table 2). Where minimum clinically significant differences are not known, a change of 10% will be considered a trigger, or in consultation with our clinicians.

**Table 2 T2:** List of triggers

	Trigger (change from participants baseline value)
Medicine data	Sedative load increase by ≥2.^13^ Anticholinergic load increases ≥2.^13^ Number of medicines contributing to each adverse drug reaction listed in the Veterans’ MATES adverse event cumulative risk calculator ≥2.^37^
Resident care record	Record of common medicine-induced symptoms, for example, constipation, dry mouth, delirium. Hospital discharge or emergency department admission in the past week.
Activity tracker	≥30 min in daily sedentary time.^14 38^
Sleep sensor	≥10% reduction in sleep quality; ≥1 hour change in sleep time.^39 40^
Blood pressure	≥10 mm Hg change in systolic blood pressure; ≥5 mm Hg in diastolic blood pressure.^41^
Weight	≥5% change in weight.^42^
Blood glucose level	≥10% change.

### Phase II

The pre-post feasibility study will be conducted over 12 weeks. The study will be reported according to the Consolidated Standards of Reporting Trials checklist for pilot and feasibility trials.^28^ The sleep sensor (Fibion Emfit)^19^ will be installed in the rooms of all enrolled and consenting residents, and study staff will provide residents with an activity tracker (Fibion SENS).^18^ Two weeks of baseline data will be collected from these technologies prior to the start of the pharmacist service.

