### Outcomes and analysis

Study outcomes will be measured at 4-week, 8-week and 12-week postbaseline period. Health outcomes include number of medication adverse events and change in resident symptom score (ESAS); surrogate measure outcomes include change in physical activity and sleep; process measure outcomes include number of pharmacist recommendations provided, record of staff time spent during study implementation period and proportion of all pharmacists’ recommendations to GPs and aged care staff that are implemented.

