#### Process evaluation to assess the feasibility of the pharmacist service

A mixed methods evaluation, applying the RE-AIM evaluation framework^30^ will be performed to assess the feasibility of the pharmacist service. Descriptive statistics will be employed to report demographic characteristics and health information obtained from the Resident Care Assessment Record.

To determine *reach*, the number and proportion of eligible residents who were willing to participate in the study will be calculated. Information that will be collected include number of residents approached by the study staff or pharmacist and provided with the study information, number of residents who meet the inclusion criteria, number of residents who provided consent and number of participants who completed the 12-week study.

To determine *effectiveness*, changes in resident symptom score predigital and postdigital pharmacist service, as measured using the ESAS, will be assessed. Changes in medication use will be assessed, including changes to sedative and anticholinergic load predigital and postdigital pharmacist service. Changes in 24-hour movement behaviour, as measured using the activity tracker, will be assessed predigital and postdigital pharmacist service. The number of adverse events including falls (both injurious and non-injurious), fractures, delirium, faecal impaction, hospitalisation or emergency department presentation due to adverse medication events and medication incidents will be assessed. The number of adverse events experienced by residents within the 12-week predigital pharmacist service versus number of adverse events experienced during the 12-week digital pharmacist service period will be compared. Pre-post paired t-test or Wilcoxon test will be used for continuous data and McNemar’s tests for categorical variables.

To assess service *adoption*, the number and proportion of organisation staff invited, that agreed to participate, will be calculated.

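### The stated study, baseline and service lengths cannot all hold, and adverse events are compared as counts with tests that ignore time at risk

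*Protocol article*

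**What the plan says.** All references are to the protocol article.

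- **Study length.** Study design describes phase II as a 12-week pre-post study. Phase II repeats it: "The pre-post feasibility study will be conducted over 12 weeks".
- **Baseline.** Phase II places it relative to the service: "Two weeks of baseline data will be collected from these technologies prior to the start of the pharmacist service". The section on triggers for review places it relative to the study: "Baseline data collected within the first 2 weeks of the study will be averaged and serve as the reference point".
- **Service length.** The abstract gives the pharmacist 12 weeks of monitoring. Outcomes and analysis counts time from the end of baseline: "Study outcomes will be measured at 4-week, 8-week and 12-week postbaseline period".
- **Comparison.** The process evaluation section sets "The number of adverse events experienced by residents within the 12-week predigital pharmacist service" against the "number of adverse events experienced during the 12-week digital pharmacist service period will be compared".
- **Tests.** The same section says "Pre-post paired t-test or Wilcoxon test will be used for continuous data", with McNemar's test for categorical variables. It mentions no rate or resident-time.
- **Cohort.** "Residents will be considered eligible to participate if they are a permanent resident living in the designated residential aged care facility". Palliative and respite care are excluded, and no minimum length of stay is set. Informed consent allows withdrawal at any time. Table 1 records deaths at 4, 8 and 12 weeks.

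**The concern.** A before-and-after comparison of event counts is fair only if residents are observed for the same time in both windows. Two features of the plan put that in doubt.

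First, the calendar does not add up. A 12-week study whose first two weeks precede the service contains a 10-week service, yet the comparison names a 12-week one. The two device weeks are not assigned to the pre window, the service window or neither.

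Second, individual exposure can differ even when the windows are nominally equal. A resident admitted shortly before enrolment has less than 12 weeks of earlier facility records. One who dies, leaves or withdraws has less than the full service period. Every participant must, however, have survived the pre window to enrol. The tests named work on each resident's count, or on any-versus-none, and cannot adjust for this.

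At stake is whether an observed change in events reflects the service or the length of observation. Under Risks, the article anticipates a reduction in adverse events, which is the direction in which a shortened service window would push the counts.

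**Working it through.** **1. Can the lengths be reconciled?** The plan's own figure is a 12-week service window.

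- Literal reading of Phase II with the triggers section: 12 study weeks − 2 baseline weeks = 10 service weeks. The 12-week figure is not reproduced.
- Reading from the abstract, Outcomes and analysis and the process evaluation: 2 baseline weeks + 12 service weeks = 14 weeks. The 12-week service is reproduced, but the total is no longer 12 weeks.
- If the whole 12-week study is taken as the post window, the lengths match, but 2 of its 12 weeks (16.7%) come before the service.

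**2. Exposure with 30 residents (Sample size), all complete.**

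- 12-week service: 30 × 12 = 360 against 360 resident-weeks; expected count ratio 1.00 with no effect.
- 10-week service: 30 × 10 = 300 against 360; ratio 300/360 = 0.833, an apparent fall of 16.7%. This ratio does not depend on the event rate.

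**3. In events.** The Introduction gives up to 27 adverse medicine events per 100 residents per month, and about one in five persons affected per month. The second is used here as 0.20 events per resident-month, which is an assumption. Both rates are illustrative. Months: 84/30.44 = 2.76 for 12 weeks; 70/30.44 = 2.30 for 10 weeks. Expected events = 30 × rate × months.

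| Rate per resident-month | 12 weeks | 10 weeks | Difference |
|---|---|---|---|
| 0.27 | 22.4 | 18.6 | 3.7 |
| 0.20 | 16.6 | 13.8 | 2.8 |

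**4. Effect on the paired t-test.** This was simulated with 20,000 runs, 30 residents, independent Poisson counts (assumption), no true effect and a two-sided 5% level. Rejection rates were 5.1% to 5.2% for 12 against 12 weeks, and 7.9% to 8.6% for 12 against 10.

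**5. Incomplete windows, with 12 against 12 weeks.** The numbers of residents are assumed; each loses half a window (6 weeks).

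| Late admissions | Leavers | Pre weeks | Service weeks | Count ratio, no effect |
|---|---|---|---|---|
| 0 | 3 | 360 | 342 | 0.95 |
| 0 | 6 | 360 | 324 | 0.90 |
| 3 | 0 | 342 | 360 | 1.05 |
| 6 | 0 | 324 | 360 | 1.11 |
| 3 | 3 | 342 | 342 | 1.00 |

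Leavers lower the ratio and late admissions raise it. With a 10-week service and 6 leavers it is 270/360 = 0.75.

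**6. Precision.** For a true ratio of 1 and independent Poisson totals, the 95% limits are exp(±1.96 × √(2/events)). With 22 events per window this gives 0.55 to 1.81.

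**The case against.** The strongest reply is that the reading with a 12-week service is the better supported. The abstract, the outcome time points and the comparison itself agree on it. Table 1 also ticks deaths in the 12-week study period at 4, 8 and 12 weeks but not at baseline, which suggests that the period starts after baseline. No passage states a 10-week service. On this view the fault is loose use of 12 weeks in Phase II, and the calendar distortion is zero. This stands in part: it removes the 16.7% figure if it is what the sponsor means. It does not remove the contradiction, because it overrides the wording of Study design and Phase II, and it still leaves the two device weeks unassigned.

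A reader might infer three stronger things that the document does not support.

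- *That baseline is placed both inside and before the study.* Phase II places it before the service, which agrees with the triggers section. A position before the 12 weeks is only implied by the outcome time points and the 12-week service.
- *That death, withdrawal and late admission will be ignored, or that only completers will be analysed.* Deaths are recorded and completers counted. Rules for incomplete follow-up may sit in an analysis plan or full protocol that is not shown. What the article does state is a comparison of numbers with tests that have no exposure term.
- *That the bias favours the service.* Only the 10-week reading has a fixed direction. Late admission and attrition act against each other.

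It is also fair to say that a paired test on per-resident counts is not wrong in itself when windows are equal, and that a count model on 30 residents with few events is not robust either.

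**Conclusion.** The concern holds in a limited form. The statements on study, baseline and service length are mutually inconsistent, and that is a matter for the protocol, not something an analysis plan can settle. The stated event comparison is also sensitive to unequal observation time in a cohort where such inequality is possible.

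The size depends on the reading. It is a spurious fall of 16.7% (about 3 to 4 events) if the service lasts 10 weeks, and no calendar distortion if it lasts 12. The further effect of incomplete windows is roughly ±5% to ±11% in the one-sided scenarios assumed above, with net direction unknown. The event figures rest on the Introduction's background rates, which may not match this facility or the plan's own list of events.

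Severity is moderate. The comparison is one of several effectiveness measures in a 30-resident feasibility study with no stated power, and its interval would be wide under any reading.

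**What to change.** 1. **Reconcile the timetable.** Study design, Phase II, the triggers section, Outcomes and analysis and the process evaluation should give one total study length, one baseline length and one service length. The choice is the sponsor's.
2. **Define both comparison windows by date** for each resident, and say which window, if any, holds the two device weeks.
3. **Compare rates instead of counts.** For each resident and window, days at risk run from the later of admission or window start to the earlier of death, departure, withdrawal or window end. Include residents who do not complete. One suitable analysis is a Poisson model with period as the effect, log(days at risk) as offset and robust standard errors clustered on resident, reporting the rate ratio with 95% CI. This would replace the paired t, Wilcoxon and McNemar tests for adverse events only. With full follow-up it returns an expected ratio of 1.00 under no effect for either service length.

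**Cost.** A few sentences and a little more analysis work. Admission and departure dates must be extracted, since Table 1 does not list them. The interval will be wide with about 17 to 22 events per window. The offset corrects for length of observation but does not remove the conditioning on having survived the pre window, which should be stated as a limitation.
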